### Safety assessment

Investigators will be required to monitor and document all adverse reactions in the case report forms (CRFs) according to predefined criteria.

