**Methods:**

This three-arm randomized controlled trial will enroll 105 patients with PSCI, randomly allocated 1:1:1 to the MAG (*n* = 35), ACU (*n* = 35), and SHM (*n* = 35) groups. Interventions will be administered 5 times/week for 3 weeks. All groups will receive high-frequency rTMS over the L-DLPFC (10 Hz, 80% rest motor threshold). The primary outcome is the Montreal Cognitive Assessment (MoCA) change from baseline to week 3. Secondary outcomes include the Mini-Mental State Examination (MMSE), Modified Barthel Index (MBI), Hamilton Anxiety Rating Scale (HAMA), Hamilton Depression Rating Scale (HAMD), Pittsburgh Sleep Quality Index (PSQI), and adverse events. Functional magnetic resonance imaging (fMRI) and functional near-infrared spectroscopy (fNIRS) data will be acquired at baseline and post 3-week treatment. Clinical data will be analyzed via SPSS 26.0 using repeated measures analysis of variance (ANOVA) to compare intergroup changes in outcomes across time points. Neuroimaging data will be processed in MATLAB R2018a. Correlation analyses will assess associations between clinical scores and neuroimaging parameters.

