**Figure 1 fig1:**
[figure not shown]
Trial flow chart. MoCA, Montreal Cognitive Assessment; MMSE, Mini-Mental State Examination; MBI, Modified Barthel Index; HAMD, Hamilton Depression Rating Scale; HAMA, Hamilton Anxiety Rating Scale; PSQI, Pittsburgh Sleep Quality Index.

**Table 1 tab1:** Details of the planned visit schedule.

Stage	Baseline period	Treatment period			Follow-up period	
TimePoint	0	Week 1	Week 2	Week 3	Week 8	Week 12
Enrollment						
Eligibility screen	×					
Informed consent	×					
Demographic characteristics	×					
Medical history	×					
fNIRS	×			×		
fMRI	×			×		
Interventions						
Magnetic Stimulation Group		×	×	×		
Acupuncture Group		×	×	×		
Sham Magnetic Stimulation Group		×	×	×		
Assessments						
MoCA	×			×	×	×
MMSE	×			×	×	×
MBI	×			×		
HAMA	×			×		
HAMD	×			×		
PSQI	×			×		
Patient safety						
Adverse events		×	×	×		

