### Withdrawal criteria

A participant will be withdrawn from the trial if any of the following conditions occur:Serious adverse reactions requiring termination, as determined by a specialist physician;Worsening symptoms or severe complications necessitating emergency measures;Identification of critical safety concerns by investigators;Voluntary withdrawal for personal, family, or social reasons that precludes completion of the treatment course.

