### Randomization and blinding

The allocation sequence is computer-generated by an independent statistician using block randomization (block size = 3) with a 1:1:1 ratio for the MAG, ACU, and SHM group. Allocation concealment is implemented using sequentially numbered, opaque, sealed envelopes. Each envelope contained an allocation card corresponding to the group assignment. Envelopes will be opened sequentially by treating physicians to deliver the allocated intervention.

Given the nature of the magnetic stimulation, acupuncture, and sham magnetic stimulation intervention therapies, it is not possible for the treating physicians to be blinded in this trial. However, participants, outcome assessors, and data analysts will be blinded to group allocation. To minimize bias, strict separation of roles is maintained between intervention operators, outcome assessors, and statisticians throughout the trial. Blinding assessment will be conducted after the final treatment session. All participants will be asked to guess their group allocation from four options: PC6 MAG, PC6 ACU, PC6 SHM, or uncertain. These responses will be used to calculate the James Blinding Index, which quantifies blinding success on a scale from 0 to 1, where 1 indicates complete blinding (all “do not know”), 0 indicates complete unblinding (all correct), and 0.5 represents random guessing (29). Given the potentially perceptible differences between active magnetic stimulation and sham stimulation, a higher risk of functional unblinding may exist between the MAG and SHM groups, which will be considered when interpreting the blinding assessment results.

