#### Secondary outcomes

Secondary endpoints comprise global cognition, functional independence, anxiety, depression, and sleep quality, each assessed with a validated instrument as detailed below.Mini-Mental State Examination (MMSE): the 30-item MMSE assesses orientation, immediate recall, attention/calculation, delayed recall, language, and visuospatial ability. Education-adjusted cut-offs are ≤17 (illiterate), ≤20 (primary education), and ≤24 (≥junior-high); lower scores denote more severe impairment (36).Modified Barthel Index (MBI): this scale is a specialized tool for evaluating activities of daily living (ADL), comprising 10 assessment items, including eating, bathing, personal hygiene, dressing, bowel and bladder control, bed-to-chair transfer, walking on level ground, wheelchair operation, and ascending/descending stairs. During the assessment, evaluators score each item based on the patient’s level of assistance required. Ten items yield a 0–100 score; lower scores indicate greater ADL dependence (37).Hamilton Anxiety Rating Scale (HAMA): this scale contains 14 items, with 7 items each for somatic anxiety and psychic anxiety. Total scores ≥7 suggest anxiety; higher scores reflect increased severity (38).17-item Hamilton Depression Rating Scale (HAMD): this scale includes 17 items, covering dimensions such as anxiety/somatization, weight change, cognitive impairment, diurnal variation, retardation, sleep disturbances, and feelings of hopelessness. Total scores ≥7 indicate possible depression; higher scores correspond to greater severity (39).Pittsburgh Sleep Quality Index (PSQI): the PSQI consists of 18 items, covering seven components: sleep onset latency, sleep duration, sleep efficiency, subjective sleep quality, sleep disturbances, use of hypnotic medications, and daytime dysfunction. The total score ranges from 0 to 21, with higher scores indicating poorer sleep quality (40).

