### Objectivity in outcome assessment and quality control

All clinical outcomes will be assessed by trained evaluators who are blinded to group allocation and not involved in treatment delivery. Assessors will follow a standardized assessment manual to minimize inter-rater variability, and role separation will be maintained between intervention operators, outcome assessors, and statisticians. Data will be recorded on case report forms and verified by independent checking to reduce entry errors, and protocol deviations as well as concomitant rehabilitation potentially affecting cognition will be documented. For neuroimaging, preprocessing and metric extraction will follow a pre-specified pipeline, with imaging analysts blinded to group allocation. Quality control will include motion/artifact inspection and predefined exclusion criteria.

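### Adverse events are the stated safety outcome, but the only collection rule covers adverse reactions, so events judged unrelated to treatment need not be recorded

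*Protocol article*

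**What the plan says.** Five places in the protocol article bear on this point.

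- **Abstract, Methods.** The list of secondary outcomes ends with "Pittsburgh Sleep Quality Index (PSQI), and adverse events".
- **Table 1.** The patient-safety row is labelled "Adverse events" and is marked at weeks 1, 2 and 3.
- **Safety assessment.** The whole section is one sentence: "Investigators will be required to monitor and document all adverse reactions in the case report forms (CRFs) according to predefined criteria".
- **Secondary outcomes.** The list is described as follows: "Secondary endpoints comprise global cognition, functional independence, anxiety, depression, and sleep quality, each assessed with a validated instrument as detailed below". Adverse events are not in it.
- **Blinding.** Under Randomization and blinding, "it is not possible for the treating physicians to be blinded in this trial", while "participants, outcome assessors, and data analysts will be blinded to group allocation". The section on objectivity in outcome assessment adds: "All clinical outcomes will be assessed by trained evaluators who are blinded to group allocation and not involved in treatment delivery".

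**The concern.** The outcome and the rule for collecting it are stated in different terms, and the rule's term is the narrower one. In ordinary trial usage an adverse event is any untoward occurrence, while an adverse reaction is one suspected of being caused by treatment. A form that collects only the second cannot yield a count of the first.

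Two things are at stake. The more certain is completeness: an event set aside as unrelated is not on the form and cannot be recovered at analysis. The less certain is comparability between arms: if the person deciding what counts as a reaction knows the allocation, that decision could differ by arm. The Discussion makes the effect of PC6 magnetic stimulation over sham a stated aim, so a sound safety record for that contrast matters.

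**Working it through.** The article gives no adverse event rates, so there is no figure of its own to reproduce. The check is first textual, then a short illustration on assumed rates.

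**1. Outcome against collection rule.** The Abstract and Table 1 use the broad term and the Safety assessment section the narrow one. Neither is defined. The Withdrawal criteria also use the narrow term, "Serious adverse reactions requiring termination, as determined by a specialist physician", and list worsening symptoms and severe complications as a separate item. That suggests, without proving, that reactions are meant as the smaller class.

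**2. Outcome list against outcome list.** The Abstract counts adverse events among the secondary outcomes; the Secondary outcomes section does not.

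**3. Who records.** If adverse events are a clinical outcome, as the Abstract implies, the objectivity section gives them to blinded evaluators. The Safety assessment section gives them to investigators, whose blinding is not stated. Treating physicians are unblinded, but the article never says that they are the investigators in question. The recorder's knowledge of the arm is therefore undetermined.

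**4. Under-counting.** Let *p* be the true event rate and *a* the probability that an event is judged related.

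- Recorded rate = *p* × *a*; share of events lost = 1 − *a*.
- Assumed example: *p* = 20% in an arm of 35 gives 35 × 0.20 = 7 events.
- With *a* = 0.7, 7 × 0.7 = 4.9 are recorded and 2.1 (30%) are lost.

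This loss occurs in every arm and needs no unblinded recorder.

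**5. Distortion between arms.** Assume the same true rate *p* in MAG and SHM, with attribution probabilities *a*₁ and *a*₀. Spurious risk difference = *p* × (*a*₁ − *a*₀).

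| True rate (assumed) | 0.7 v 0.7 | 0.8 v 0.5 | 0.9 v 0.3 |
|---|---|---|---|
| 10% | 0 | 3 points | 6 points |
| 20% | 0 | 6 points | 12 points |
| 30% | 0 | 9 points | 18 points |

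For example, 0.20 × (0.9 − 0.3) = 0.12. If every event is recorded, *a*₁ = *a*₀ = 1 and the spurious difference is 0. None of these rates comes from the documents.

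**6. Where unequal attribution is plausible.** All arms receive active L-DLPFC rTMS with each session (Intervention and grouping). A headache could therefore be put down to treatment in any arm, even by someone who knows the allocation. Local effects at PC6 are different: in SHM the coil is reversed and its output set to zero, so an operator who knows this might discount a forearm complaint there but not in MAG.

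**The case against.** The strongest reply is that this is loose wording in a condensed article. The Safety assessment sentence asks for all reactions and refers to criteria fixed in advance that the article does not show; those criteria may cover every event. The Abstract and Table 1 use the broader term, so the authors may treat the two as synonyms. This is possible, and it is why no biased record can be asserted. It does not reconcile the rule as written with the outcome as written: the reference to criteria says how reactions are documented and does not widen the class.

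A reader might go further and infer that investigators who know the arm filter events by presumed cause before recording, so that the MAG versus SHM safety comparison is biased. The documents do not support that. They describe no causality step before recording, they do not identify the recorder with the unblinded treating physicians, and the objectivity section can be read as giving the task to blinded evaluators. The size of any distortion rests wholly on assumed attribution rates.

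A reader might also infer that withdrawal for serious reactions depends on the same incomplete record. It need not: that criterion is left to a specialist physician's judgement, with no reference to the case report form, and other withdrawal criteria are not limited to reactions.

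It is also fair to say that form design and safety tabulations usually sit in fuller documents. Their absence here is not the point; the point is what the collection rule states.

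**Conclusion.** The inconsistency is real. As written, the collection rule does not deliver the secondary outcome named in the Abstract and scheduled in Table 1, and the two lists of secondary outcomes disagree. Taken literally, the rule under-counts adverse events in all arms by the share judged unrelated, a proportion that the documents do not give. This rests on the ordinary meaning of the two terms and on the unshown criteria not widening the rule.

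Bias between arms is a possibility, not a finding. It needs a recorder who knows the arm and attribution that differs by arm, and neither is established. With equal true event rates, the spurious difference is zero under equal attribution and 3 to 18 points under the unequal splits assumed above.

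The matter is worth correcting before data collection because unrecorded events cannot be restored later. It does not touch the primary MoCA analysis.

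**What to change.** 1. Reword the Safety assessment section so that all adverse events are recorded in every arm regardless of presumed cause, with relatedness entered in a separate field.
2. Make the between-arm safety comparison on all events.
3. State whether the person recording adverse events is blinded. If not, limit the blinded-evaluator claim in the objectivity section to the rating scales.
4. Add adverse events to the Secondary outcomes section so that it agrees with the Abstract.

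The cost is protocol wording and one case report form field. The downside is somewhat more events to record, some of them unrelated to treatment. The proposal concerns data collection only; it changes neither treatment nor the withdrawal criteria.

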### Imaging data acquisition

#### MRI data acquisition

All MRI examinations will be performed at the MRI Center of West China Hospital, Sichuan University, on a 3.0 T scanner (Discovery MR750; GE Healthcare, Milwaukee, USA) equipped with an eight-channel phased-array head coil. Before scanning, each participant will be screened for contraindications and asked to remove all metallic items. Foam cushions will be placed around the head to minimise motion, and earplugs will be provided to attenuate acoustic noise. Scans will be acquired with the participant lying supine and remaining alert throughout.

A high-resolution structural dataset will be obtained with a three-dimensional T1-weighted spoiled gradient-echo sequence: repetition time/echo time (TR/TE) = 6.2/2.5 ms, field of view = 256 × 256 mm^2^, matrix = 256 × 256, voxel size = 1.0 × 1.0 × 1.0 mm^3^. BOLD images will be acquired using a gradient echo planar imaging (GRE-EPI) sequence: TR/TE = 2000/30 ms, flip angle = 90 degrees, slice thickness = 2 mm, field of view (FOV) = 128 × 128 mm^2^, voxel size = 2 × 2 × 2 mm^3^. DTI sequences will be acquired FOV = 256 × 256 mm^2^, TR = 6,500 ms, matrix = 128 × 128, number of diffusion-encoding directions = 32, slice thickness 2 mm, layer spacing = 0, and gradient values b = 0 s/mm^2^ and b = 1,000 s/mm^2^.

#### fNIRS data acquisition

This study will employ fNIRS to repeatedly acquire patients’ brain functional activity at three time points (before the first treatment, after the first treatment, and after the last treatment). Data will be collected using an fNIRS system (NIRSCAN, Huichuang, China) with wavelengths of 740 nm and 850 nm, consisting of 48 effective channels (22 light source probes and 16 detector probes). Cortical hemodynamic changes will be sampled at 11 Hz, with 3 cm inter-channel spacing covering the frontal and parietal lobes.

During data acquisition, the assessment room will be kept quiet, with only the patient and examiner present. The patient will be seated upright with head immobilized, and the probe array will be secured to the scalp. After probe adjustment and verification of optimal signal quality across all channels, data collection will began. The Verbal Fluency Test (VFT) (41) will be used as the cognitive activation task. As a validated measure of executive function, VFT reflects complex cognitive processes and has been extensively used in fNIRS research (42). Each trial will comprise a 60-s pre-task baseline, a 60-s task period (divided into three 20-s blocks), and a 60-s post-task recovery period. During the task, participants will generate as many words as possible based on three randomly presented Chinese characters (e.g., ‘Jiang’, ‘Ri’, ‘Da’), with the number of valid words recorded as a measure of cognitive performance.

Based on potential factors such as patient intolerance to imaging procedures, imaging data quality issues, or other possible interfering factors, we anticipate an imaging attrition rate of approximately 10%.

### Objectivity in outcome assessment and quality control

All clinical outcomes will be assessed by trained evaluators who are blinded to group allocation and not involved in treatment delivery. Assessors will follow a standardized assessment manual to minimize inter-rater variability, and role separation will be maintained between intervention operators, outcome assessors, and statisticians. Data will be recorded on case report forms and verified by independent checking to reduce entry errors, and protocol deviations as well as concomitant rehabilitation potentially affecting cognition will be documented. For neuroimaging, preprocessing and metric extraction will follow a pre-specified pipeline, with imaging analysts blinded to group allocation. Quality control will include motion/artifact inspection and predefined exclusion criteria.

### Statistical analysis

#### Clinical data analysis

All analyses will be performed using SPSS 26.0 (IBM, Armonk, NY, USA) with two-tailed tests (*p* < 0.05). Quantitative data will be expressed as mean ± standard deviation. Within-group comparisons will use paired t-tests. Between-group comparisons will employ one-way ANOVA or nonparametric rank-sum tests (Kruskal-Wallis test), depending on data distribution. Count data will be presented as numbers (percentages), to be analyzed by *χ*^2^ tests, Fisher’s exact tests, or Ridit analysis. Repeated-measures ANOVA with Greenhouse–Geisser correction will be applied to evaluate longitudinal changes across timepoints. Both intention-to-treat (ITT) and per-protocol (PP) analyses will be conducted. In the ITT analysis, missing outcome data will be handled using multiple imputation under the assumption of missing at random. For the primary outcome (MoCA), we will report effect sizes and 95% confidence intervals for between-group differences in score changes. Clinical relevance will be interpreted using published MoCA change ranges and distribution-based benchmarks, rather than a prespecified minimal clinically important difference (MCID). Pearson’s or Spearman’s correlation coefficients (selected based on data distribution) will be calculated to examine associations between clinical scales and neuroimaging parameters. Covariates including age, sex, years of education, time from stroke onset to study enrollment, and a quantitative metric capturing the “dose” of conventional rehabilitation (derived from documented type, frequency, and duration), and lesion side (left/right) will be incorporated into a multivariate linear regression model evaluating the primary endpoint (change in MoCA score) and key secondary cognitive outcomes. Furthermore, to explore the potential modifying effect of lesion side on treatment response, we will conduct an exploratory analysis by adding a Group × Lesion Side interaction term to the primary multivariate model for the MoCA change score and key imaging outcomes. These interaction analyses will be explicitly labeled as exploratory, and their results will be interpreted cautiously due to the limited statistical power for detecting interaction effects.

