### Inclusion criteria

Aged 30–75 years, right-handed;Definite history of stroke, with clinical and imaging evidence supporting the diagnosis;Presence of impairment in one or more cognitive domains, with a MoCA score <26;Stable vital signs;Written informed consent from the patient or legal guardian.

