### Sample size

This study employes a three-arm, parallel-group, randomized controlled design (1:1:1 allocation), with the MoCA score as the primary endpoint. One-way analysis of variance (ANOVA) is used to compare differences among the three groups. Due to the lack of a clear anticipated effect size, based on previous rTMS studies in PSCI (26–28), we adopt Cohen’s f ≈ 0.32 as the expected effect size. Using G*Power 3.1 (test type: one-way ANOVA; effect size *f* = 0.32; *α* = 0.05, two-tailed; power = 0.80), the estimated total sample size is 99 (33 per group) to detect significant differences in MoCA scores. To account for a potential 10% attrition rate, the final recruitment target is set at 105 participants (35 per group). Because *a priori* information on within-subject correlation and covariate R^2^ was unavailable, we used one-way ANOVA for conservative planning. The primary analysis will use longitudinal models with covariate adjustment, which is expected to provide equal or greater efficiency than the planning model.

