### Outcomes

#### Primary outcome measurement

This study will use changes in Montreal Cognitive Assessment (MoCA) scores before and after treatment as the primary outcome measure. The MoCA is a comprehensive cognitive assessment tool that covers seven domains (visuospatial/executive function, naming, attention, language, abstraction, delayed recall, and orientation). The total score is 30, with a cutoff value of 26. A score below 26 indicates cognitive impairment, and the lower the score, the poorer the cognitive ability (35).

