## Limitations

This single-center exploratory trial has several limitations. Firstly, although the L-DLPFC was selected as the target region, target localization was implemented via cap-based approaches (the “5-cm rule”) rather than neuronavigation techniques. Previous studies have demonstrated the imprecision of the “5-cm rule” for rTMS stereotactic localization, with evidence showing that this method may result in stimulation over non-prefrontal regions in a substantial proportion of subjects (64–66). This cap-based approach may therefore induce inter-individual localization variability and potentially compromise the internal validity of the trial. Secondly, clinical heterogeneity in PSCI may still influence treatment response. While key factors such as stroke subtype, lesion characteristics, and time from stroke onset to enrollment will be documented and explored as covariates in multivariable and sensitivity analyses, the trial may be not powered for definitive subgroup analyses. Thirdly, the use of a single acupoint (PC6, Neiguan) enhanced the rigor of experimental control, yet it deviates from routine clinical practice where multi-acupoint acupuncture is the standard modality. Thus, extrapolation of the study results to real-world settings should be performed with caution. Fourthly, despite efforts to optimize masking, blinding may be imperfect due to the distinct somatosensory experiences between acupuncture and magnetic stimulation, which may introduce expectation-related bias. Finally, the follow-up duration is relatively short, which limits conclusions regarding the long-term durability of cognitive and network-level changes; larger multicenter trials with longer follow-up will be necessary to confirm sustained clinical benefits.

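### The primary model for MoCA change does not name baseline MoCA as a covariate, which forgoes precision that the collected data could supply and leaves the efficiency expectation unsecured

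*Protocol article*

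**What the plan says.** The Primary outcome measurement section states: "This study will use changes in Montreal Cognitive Assessment (MoCA) scores before and after treatment as the primary outcome measure". The Abstract fixes the interval as baseline to week 3.

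Clinical data analysis then sets out the adjusted model. The list starts "Covariates including age, sex, years of education, time from stroke onset to study enrollment, and a quantitative metric capturing the" dose of conventional rehabilitation and ends with lesion side. These terms "will be incorporated into a multivariate linear regression model evaluating the primary endpoint (change in MoCA score) and key secondary cognitive outcomes". An exploratory Group × Lesion Side term is added to the same model. The Limitations section mentions further factors (stroke subtype, lesion characteristics) that "will be documented and explored as covariates in multivariable and sensitivity analyses". Baseline MoCA is named as a covariate in none of these places, although Table 1 schedules MoCA for everyone at time 0.

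The same section plans one-way ANOVA or Kruskal-Wallis tests between groups and repeated-measures ANOVA over time. In the latter, baseline enters as one of the time points.

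On planning, Sample size says: "One-way analysis of variance (ANOVA) is used to compare differences among the three groups". It uses f = 0.32, notes that the within-subject correlation and covariate R² were not available, and says the primary analysis will be a covariate-adjusted longitudinal model, "which is expected to provide equal or greater efficiency than the planning model".

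**The concern.** In a randomised trial with a baseline measurement of the outcome, the usual way to compare change between arms is to adjust for that baseline. An unadjusted change score subtracts the whole baseline value, whatever the correlation between the two measurements. When the correlation is below 1 and the SDs are equal, that over-corrects and adds noise.

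Two things are at stake. The first is precision in a trial planned at 33 evaluable patients per arm with power just above 0.80. The second is how one realised dataset reads: if the MAG arm happens to start lower than the SHM arm, it will tend to show a larger gain for that reason alone. The named covariates address this only so far as they predict baseline MoCA.

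Repeated-measures ANOVA does not supply the adjustment. With baseline and week 3 only, its Group × Time test is the unadjusted comparison of change scores.

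**Working it through.** **Inputs from the document.** Three arms, 1:1:1; f = 0.32; α = 0.05; target power 0.80; N = 99 evaluable, 105 recruited (35 per arm).

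**Inputs assumed.** Correlation ρ between baseline and week-3 MoCA (none is given); the ratio of baseline to week-3 SD; a baseline MoCA SD of 4 points (range 3 to 5).

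**1. The plan's own figure.** Noncentral F with noncentrality N·f², df 2 and N-3: at N = 99, 99 × 0.32² = 10.14 and power is 0.808. The smallest N reaching 0.80 is 98, or 99 in multiples of three. The stated 99 reproduces.

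**2. Variance with and without baseline.** With a common SD s:

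- unadjusted change: 2(1-ρ)s²
- baseline-adjusted: (1-ρ²)s²
- ratio adjusted/unadjusted: (1+ρ)/2, so the information forgone is (1-ρ)/2.

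If f = 0.32 refers to change, the adjusted f is 0.32/√((1+ρ)/2). Power uses one fewer denominator df. The unadjusted power is 0.808 throughout.

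| ρ (assumed) | Variance ratio | Information forgone | Adjusted f | Power at 99 | Adjusted N matching 99 unadjusted |
|---|---|---|---|---|---|
| 0.5 | 0.75 | 25% | 0.370 | 0.910 | 75 |
| 0.7 | 0.85 | 15% | 0.347 | 0.870 | 85 |
| 0.8 | 0.90 | 10% | 0.337 | 0.850 | 90 |

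**3. Unequal SDs.** With q = baseline SD / week-3 SD, the loss is 1 - (1-ρ²)/(1+q²-2ρq).

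| ρ | q = 0.8 | q = 1 | q = 1.2 |
|---|---|---|---|
| 0.5 | 11% | 25% | 40% |
| 0.7 | 2% | 15% | 33% |
| 0.8 | 0% | 10% | 31% |

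The loss is never negative, but its size depends on quantities that the document does not give. None of these figures credits age or education with carrying part of the baseline information; where they do, the gain is smaller.

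**4. Chance imbalance.** With equal SDs, a baseline difference d between two arms leaves an error of about -(1-ρ)d in the change contrast: 0.5, 0.3 or 0.2 MoCA points per point of difference at ρ = 0.5, 0.7 or 0.8. The SE of d at 35 per arm is SD × √(2/35) = 0.72, 0.96 or 1.20 for SD 3, 4 or 5. So |d| is at least 1 point in 16%, 30% or 40% of trials.

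**5. The efficiency expectation.** Its comparator is the planning one-way ANOVA.

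- If f refers to change: six covariates that explain nothing move power from 0.808 to 0.807, so the expectation essentially holds.
- If f refers to the MoCA score itself: the change-score f is 0.32/√(2(1-ρ)) and the adjusted f is 0.32/√(1-ρ²).

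| ρ | Change-score power | Baseline-adjusted power | Covariate R² needed to match the planning ANOVA |
|---|---|---|---|
| 0.3 | 0.657 | 0.845 | 0.29 |
| 0.4 | 0.728 | 0.874 | 0.17 |
| 0.5 | 0.808 | 0.910 | 0 |
| 0.7 | 0.961 | 0.982 | none |
| 0.8 | 0.996 | 0.998 | none |

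The R² column is 1 - 1/(2(1-ρ)). The expectation fails only for ρ below 0.5 combined with an R² below that column.

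**The case against.** Four points can be made for the plan, and each has some force.

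- **The list is open.** It begins with a word that allows further covariates, and the full protocol and any SAP are not shown. So this is a failure to name baseline MoCA, not a decision to exclude it. That stands. But the article names the primary model's covariates down to a rehabilitation metric. Leaving out the outcome's own baseline means its use is either absent or still to be settled.
- **The efficiency sentence may be true.** A reader might infer that the plan breaks its own promise. The document does not support that. The sentence states an expectation against one-way ANOVA, and for ρ from 0.5 to 0.8, the range that gives a 25% to 10% loss, the change score equals or beats an ANOVA on post-treatment scores.
- **The loss is not a known quantity.** A reader might take 10-25% as fact. It needs both an assumed ρ and equal SDs. Entry requires "Presence of impairment in one or more cognitive domains, with a MoCA score <26", and that ceiling could narrow the baseline SD. At q = 0.8 the loss falls to 11%, 2% and 0%. Nor does the document show that baseline MoCA is the strongest predictor of change.
- **Imbalance is not bias.** Randomisation keeps the unadjusted contrast unbiased on average, and its confidence interval already allows for chance imbalance. The conditional error is the same precision loss seen from within one dataset, not a second defect.

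For the secondary scales, baseline does enter the planned repeated-measures ANOVA as a time point, so it is not ignored. It is still not used as a covariate.

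**Conclusion.** The point holds in a limited form. The primary regression names six covariates and omits baseline MoCA, and no other planned analysis supplies that adjustment. With equal SDs the information forgone is 25%, 15% or 10% at assumed ρ of 0.5, 0.7 or 0.8. Across SD ratios of 0.8 to 1.2 it runs from near 0 to about 40%, before any credit to age and education. With f on the change scale, power at N = 99 would go from 0.81 to about 0.91, 0.87 or 0.85 under equal SDs.

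The efficiency expectation is neither refuted nor guaranteed. It fails only if f refers to the MoCA score, ρ is below 0.5, and the listed covariates explain too little. Sample size cannot rule this out, because it words its target in terms of MoCA scores and says the correlation was unavailable. The change is worth making because it costs almost nothing, not because the planned analysis is invalid.

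**What to change.** In Clinical data analysis:

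- add baseline MoCA to the covariates of the primary MoCA change model;
- carry it into the Group × Lesion Side model for MoCA change;
- for MMSE, MBI, HAMA, HAMD and PSQI, base the between-group comparison on a model that includes the scale's own baseline value.

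In Sample size, attach the efficiency sentence to this baseline-adjusted model, and state whether f = 0.32 refers to the MoCA score or to its change.

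Cost: analysis wording and one degree of freedom per model. The baseline values are already scheduled in Table 1, so no new visits, data or patients are needed.
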